### **Analysis**

*Motivation Tool:* All quantitative data will be double entered into CsPRO. Checks will be run to identify missing data and any anomalies. Data will be exported to STATA to carry out the quantitative analysis. The characteristics of health workers and their places of work will be presented for each district to identify any significant differences that may lead to bias. The difference in mean scores from the motivation of HW tool before the intervention and after will be analysed using ANOVA to identify any significant differences (shown with 95% CIs and p values). Regression analysis will be used to identify the influence of various variables on the main outcome of staff motivation. For example, difference due to gender, age, level of health worker, place of work (hospital, PHCC, HP, SHP). Factors such as other HR initiatives or health systems changes will also be recorded and included in the analysis as they potentially be confounders.

*Routine Health Service Data:* Frequency tables with proportions will be used to compare secondary outcomes across districts. Where possible trend data from health sector annual reports over the last 5 years will be used to avoid over interpretation of data peaks.

*Qualitative data:* Ritchie and Spencer’s ‘framework’ approach will be used to analyse the qualitative data.^12^ The advantage of this structured approach is that the thematic framework can be closely based on the research objectives but also allows for other themes to emerge from the data. The transparent structured approach supports collaborative analysis. There are 5 key stages within framework approach:

1. Familiarisation: Here the analyst reads through transcripts and notes pulling out key ideas and starting to identify recurrent themes. This process will be done by two HERD researchers independently.
2. Identifying a thematic framework: In this step of the process a framework is constructed based on issues from the original research aims, emergent issues from the participants and the recurrent themes identified during the familiarisation process. At this point the cross-cutting themes of motivation, gender, management styles, other health system issues within the framework to see how perceptions and issues differ across these groups. The 2 LSTM ([name]) consultants will work with HERD researchers to develop the framework.
3. Indexing: Here the thematic framework is applied to the data.
4. Charting: this process involves lifting data from the original context and placing it within the appropriate thematic categories within the framework.
5. Mapping and interpretation: The final stage in the process is to interpret and map the range, differences and similarities within the data presented in the charts.

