### **Sampling**

Measuring Change in Motivation: Sample Size Calculation

The piloting of the motivation tools will provide more appropriate Nepal-specific information such as between individuals standard deviation (s.d.). However, for the purposes of planning the Mbindyo et al’s scale has been used to estimate the required sample size in order to detect a psychologically/clinically significant difference before the intervention and 20 months later.^1^ Mbindyo et al found a between individuals s.d. of 11 units.^44^ The mid-point of the Mbindyo et al scale is 30.- Assuming a 10% change (i.e. 3 points) is of clinical/ psychological significance then across the three districts, a random sample of 280 health workers will be invited to complete the motivation questionnaire at baseline; a different random sample of the same size will be selected post-intervention.  Assuming around a 10% refusal rate, this should provide 250 analysable questionnaires at both assessment times.  The mid-point of the motivation scale is 30 points; assuming a standard deviation of 11 points, this sample size will provide 86% power to detect a mean change in mean motivation score from baseline to post-intervention of 10% (3 points), with an alpha level of 5%.  The detectable change in mean score, with 90% power, at each of the participating districts is: Rasuwa 16% (4.7 points); Dang 18% (5.3 points); Baitadi 25% (7.5 points).

Table 7: Sample size of health workers in three districts

| **District** | **Region/ecology** | **Required Sample**  **Size** |
| --- | --- | --- |
| Rasuwa | Central/Mountain | 51 |
| Dang | Mid western/Plain (Terai) | 100 |
| Baitadi | Far western/Hill | 129 |
|  | Total | 280 |

Sampling of Health Facilities

In order to provide a spread of the required sample size across the different health facility levels, half of the total number of each level of health facility will be sampled. The required number of sampled health facilities will be recruited to give a spread based on high, low and moderate performance. This sampling process will be done in close collaboration with the DPHOs office in each district.

From these facilities the required sample of health workers will be recruited. Recruitment will be monitored to ensure that there is the required representation of the different levels of health facilities, health worker cadre and gender balance. If any of these groups appear to be disproportionately being recruited then remedial action will be taken.

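### The before-after ANOVA and the 86% power treat workers as independent although they are recruited within 65 revisited facilities, and place-of-work comparisons overstate precision

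*Protocol*

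**What the plan says.** Sampling of Health Facilities (Protocol, Sampling) sets a first stage in which "half of the total number of each level of health facility will be sampled". Workers are then recruited from those facilities. Table 8 lists 10 facilities in Rasuwa, 20 in Dang and 35 in Baitadi, 65 in all: 3 hospitals, 5 PHCCs, 21 health posts and 36 sub health posts. Step 4 returns to the same facilities at end line, without linking individuals.

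The sample size text gives "assuming a standard deviation of 11 points", a 3-point target and about 250 analysable questionnaires per round, and concludes that "this sample size will provide 86% power to detect a mean change in mean motivation score from baseline to post-intervention". It mentions no ICC or design effect.

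For the motivation tool, the Analysis section says: "The difference in mean scores from the motivation of HW tool before the intervention and after will be analysed using ANOVA", with 95% CIs and p values. It then plans a regression to find which variables influence motivation, with gender, age, level of worker and place of work as examples, and includes other HR initiatives and system changes as potential confounders. On bias it says: "The characteristics of health workers and their places of work will be presented for each district to identify any significant differences".

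**The concern.** Colleagues in one facility share an in-charge, a community and, under this intervention, one group monitoring visit and one action plan. Their scores are likely to be correlated, and change may differ from facility to facility. An analysis of individual scores without a facility term, and a power figure without a design effect, do not match that structure.

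Motivation is the main quantitative outcome, and the cost-effectiveness figure is cost per change on the tool, so the before-after estimate and its interval carry much weight. Place of work is a property of the facility. A comparison of hospitals with other levels rests on 3 hospitals, not on the 46 or so workers in them.

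The two rounds are also separate samples. If their staff mix differs, the plain difference in means shifts, and the protocol does not say that its regression supplies the adjusted before-after estimate.

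**Working it through.** **1. The stated power.** Inputs from the Sampling section: SD 11, difference 3, 250 per round, alpha 5% (two-sided assumed, since this reproduces the figure).

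SE = 11 × √(2/250) = 0.984; 3/0.984 = 3.049; power = Φ(3.049 − 1.96) = 86.2%.

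This matches 86%, so the figure contains no design effect.

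**2. Facility sizes.** Table 8 facility counts, with Table 5 staff per facility (20, 9, 5, 3), give 67, 103 and 148 available workers, as Table 8 states. Scaling to the required samples (51, 100, 129) and then by 250/280 gives:
- mean per facility per round: 250/65 = 3.85
- size-weighted mean: m = Σs²/Σs = 1511.2/250 = 6.04

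**3. Before-after contrast.** With ICC ρ and correlation c of facility effects between rounds (neither is in the protocol; both are assumed):

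DE = 1 + (m − 1)ρ − mρc

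power = Φ(3/(11√(2·DE/250)) − 1.96)

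true type I error of the naive 5% test = 2(1 − Φ(1.96/√DE))

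| ρ | c | DE | Power | Naive type I error |
|---|---|---|---|---|
| 0.05 | 0 | 1.25 | 77.8% | 8.0% |
| 0.05 | 0.5 | 1.10 | 82.8% | 6.2% |
| 0.05 | 0.8 | 1.01 | 85.8% | 5.1% |
| 0.05 | 1 | 0.95 | 87.9% | 4.4% |
| 0.10 | 0 | 1.50 | 70.1% | 11.0% |
| 0.10 | 0.5 | 1.20 | 79.4% | 7.4% |
| 0.10 | 0.8 | 1.02 | 85.5% | 5.2% |
| 0.10 | 1 | 0.90 | 89.5% | 3.9% |

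For example, at ρ = 0.05 and c = 0, DE = 1 + 5.04 × 0.05 = 1.25. The power figures assume an analysis that allows for facility. The interval multiplier √DE runs from 0.95 to 1.23 over this table.

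**4. Place of work, one round.** Hospitals: about 46.5 workers in 3 facilities, size-weighted 15.65 each. Health posts: about 81.4 workers in 21 facilities, size-weighted 3.91 each.

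At ρ = 0.05:
- hospital mean: DE = 1 + 14.65 × 0.05 = 1.73
- health post mean: DE = 1 + 2.91 × 0.05 = 1.15
- variance ratio of the contrast = (1.732/46.5 + 1.146/81.4)/(1/46.5 + 1/81.4) = 1.52
- type I error = 2(1 − Φ(1.96/√1.52)) = 11%

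At ρ = 0.10 the design effects are 2.46 and 1.29, the ratio is 2.04 and the type I error is 17%.

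If the two rounds are pooled and facility effects are fully stable, the DE of the hospital mean at ρ = 0.05 rises to 1 + (2 × 15.65 − 1) × 0.05 = 2.51. Stability helps the before-after contrast but makes this comparison worse.

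**5. Overlap of individuals.** The baseline takes 280 of about 318 available workers, leaving about 38 unsampled in those facilities. Unless turnover is high, many end-line respondents will have answered before, unlinked. If a share p overlaps with within-person correlation r, the variance of the difference is multiplied by about 1 − pr. With assumed p of 0.4 to 0.6 and r = 0.3, that is 0.88 to 0.82.

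**The case against.** The case against is substantial, and much of it stands.

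- **The 86% is not an arithmetic error.** It follows from its own inputs. What is missing is support for the independence behind it.
- **A reader might infer that the ANOVA interval is bound to be too narrow.** The documents do not support that. The same facilities are revisited, so stable facility effects cancel. At 80% stability the design effect is about 1.01 to 1.02, and at full stability the naive interval is slightly too wide. Unlinked repeat respondents push the same way.
- **A reader might infer that sample mix is ignored.** It is not. The regression names gender, age, level of worker and place of work, and the Sampling section monitors recruitment by facility level, cadre and gender. What remains is narrower: the regression is not said to give the adjusted before-after estimate, and the bias check is laid out by district with no mention of round.
- **The place-of-work p values come from the regression, not from the ANOVA.** Findings on what works in which context also draw mainly on case studies and qualitative data. The sample holds 3 of 4 hospitals and 5 of 6 PHCCs (Tables 5 and 8), close to a census of these districts. That is a reason to describe these levels; it does not justify p values that treat their workers as independent.
- **Modelling detail may sit in an analysis plan that is not shown, and an ANOVA can carry a facility factor.** That is fair in general. But this protocol names the method and states the power, and the power has no allowance for facility.

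**Conclusion.** The point holds as a mismatch between the stated sampling and the stated analysis and power. The 86% should be read as a figure under independence. Over an assumed ICC of 0.05 to 0.10, power is 70-78% with facility effects unrelated between rounds, 79-83% with half stability, about 86% with 80% stability and 88-90% with full stability. The protocol gives neither ICC nor stability, so no single corrected figure can be stated, and the error in the before-after interval may go either way.

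The place-of-work comparison is different. Its precision is overstated under any positive ICC: about 11-17% type I error for hospital versus health post in one round at ICC 0.05 to 0.10, and the problem grows if rounds are pooled with stable facility effects.

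The gap on adjustment is one of wording: which model yields the reported before-after change is not fixed.

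**What to change.** 1. Replace the ANOVA with one regression of score on round, adjusted for district, facility level, cadre, gender and age, with random effects for facility and facility-by-round. Facility-clustered standard errors over the 65 facilities are an alternative for the round effect. Name the round coefficient with its 95% CI as the main result.
2. Treat hospital and PHCC comparisons as descriptive, or take them from the mixed model with a small-sample correction. Clustered standard errors are unreliable for a comparison resting on 3 hospitals.
3. Tabulate worker characteristics by round within district.
4. State that the 86% holds only under independence, and show power over a range of ICC and between-round stability, as in the table above.

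The cost is protocol wording and a facility code on each questionnaire. The models are standard in STATA, which the protocol already names, and no extra participants are needed. The downside is that intervals may be somewhat wider and the stated power less favourable.

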# Project summary

A remarkably effective initiative to improve health worker performance was developed by a District Health Officer in a hill district (Doti) of Nepal in 2009. This study will generate further understanding of this model and replicate an improved version of the model it in different ‘intervention’ contexts (mountain, hill, and plains districts). A multi-method process evaluation will be used to document the development and implementation processes involved, assess effectiveness and scale-up feasibility.

*Aim:* To assess the processes and effectiveness of a health workforce performance model (HWPM) in improving staff performance and health outcomes and its scalability in Nepal

*Objectives:*

1. To identify lessons from Doti District pilot intervention on improving effectiveness and efficiency of health workers and develop an understanding of what worked, how and why;
2. To analyse the context in the 3 intervention districts (mountain, hill and plains) and ascertain implementation issues and strategies
3. To develop, refine and test a HWPM model in 3 different districts, assess processes, effectiveness and scalability

*Intervention:* The key components of the HWPM in Doti included: group monitoring and assessment; individual appraisal; supportive supervision and feedback; development of outcome focused job aid of health workers, and community assessment. We will conduct a process evaluation of the HWPM experience in Doti, followed by a contextual analysis of intervention districts (3). An interactive workshop with policy makers, district staff, community and health professional organisations, informed by the process evaluation of the pilot, contextual analysis in the 3 intervention districts and a review of international experience of similar initiatives, will be used to develop a contextually feasible HWPM. Following orientation of district managers the improved HWPM will be implemented in the 3 intervention districts.

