*Methods:* This is an implementation research, using a mixed method process evaluation. Qualitative approaches will include in-depth interviews, focus group discussion, ethnographic observations, and participatory observation techniques. These techniques, together with an analysis of relevant routine health service data, will generate an in-depth understanding of the context, implementation processes and changes in context during implementation in districts and at national level. Analysis of data through time, including base-line and endline data collection will support further understanding of implementation issues. Changes in staff motivation will be measured before and after the intervention using a tool which will be adapted to the Nepal context following the Doti process evaluation for assessing health worker motivation and satisfaction drawing on existing validated tools.^1,2^ Baseline quantitative data on health service delivery outcome indicators will be collected using record review of district-level facility data; implementation evaluation (inputs and outputs) and their relevance with respect to attaining desired outputs; in-depth understanding of changes in outputs (what worked or otherwise and why and how); and detailed documentation of overall factors that facilitated and hindered the intervention, and plausibility of scalability of the intervention will be documented.

*Study site:* Purposive selection of 3 districts, one from each ecological zone (mountain, hill and plains).

*Expected Outcomes:*

*Understanding what works where, why and how:* A tested and improved HWPM, documented understanding of the processes involved in the HWPM in Doti and the 3 different implementation districts; a HWPM implementation guide and training manuals

*Anticipated effectiveness outcomes:* increased motivation of health care workforce delivering quality health care services, increased functionality of health facility and reduction in staff absenteeism*;* Improved health service delivery outcomes (i.e. maternal and child health)

*Tentative time frame:* 24 months in total: process evaluation of the pilot and contextual analysis of implementing district 1-6 month; develop materials and tools for intervention package 7-8 month; intervention and process evaluation 9-20 month; final evaluation and write-up 21-24 month.

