## Study design/ methodology

It is a mixed methods intervention research with a focus on process evaluation using qualitative approaches. The effectiveness of the model will be compared using baseline and end-line data on health workers’ motivation and health service delivery outcome indicators. The processes followed during implementation and the influence of context will be explored in depth in 16 case studies covering all levels of facility in each of the districts.

##

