#### *Step 1.1: Lessons Learned in Doti*

In order to understand the context and how and why the model worked so well in Doti, the study will use a mixture of quantitative and qualitative methods.

- **Document Review**: Documents highlighting HR systems and developments over the time the model was first developed will be analysed in particular looking for systems changes and processes that may have been put in place and any reactions to these from any part of the health economy. Assess the number and cadre level of locally contracted and temporary staff, the transfer of staff, any absenteeism and functionality of the facilities.
- **Analysis of Routine Data**: Routine data will be assessed to look at changes in the health outcomes we have identified above and comparison with similar districts to see any possible improvements. At least 5 years of data will be assessed to determine any changes over the period of the intervention. This will also help us to test the feasibility of collecting this data and adapt any tools or processes to ensure that data collection during the main implementation of the model is effective.
- **Pilot the health worker motivation** tools with a range of health workers.^1,2^ As neither of these tools have yet been used in Nepal, we are keen to pilot both the tools and identify which one works best in the Nepal context. It may be that a combination of the two tools is developed that best covers all aspects of staff motivation.

Doti has approximately 217 staff spread across 2 public hospitals, 2 primary health care centres, 10 health posts and 39 sub health posts. As the use of the tool in Doti is only a pilot, a formal sample size calculation is not required, instead 30% of the total number of health workers (217) in the district will be sampled (65). The tools will be used with staff of different levels and genders to understand any issues in its implementation. The following participants will be recruited to fill the motivation questionnaires:

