- Perceptions of the group monitoring and community assessment – how do they feel about this process, how does it affect their motivation, work pattern, sense of purpose.
- Opinions on new job aids – have they had any impact on the individual and their working practices
- Any experiences or issues arising in the workplace relation to gender, caste, ethnicity, type of contract or other individual characteristic.

***In-depth interviews with HFMC members*** particularly women and those of disadvantaged caste/ethnicity groups. If possible the researchers will also observe HFMC meetings in the case study heath facilities in order to triangulate with the findings of the interviews.

Purpose of the interviews with HFMC members:

- To assess the functionality and role of the HFMC
- To explore how far the HFMC is in touch with and responsive to community needs
- To explore their perceptions of any changes in the health workers and functioning of the facility in light of the HR model implementation.

*Focus groups with community members* delineated by gender, case and ethnicity

Purpose of the community FGDs:

- To hear their views on the HFMC, how far it represents their health needs
- To explore the knowledge of and experience of the community assessments done during group monitoring
- To explore their perceptions of any changes in the health workers and functioning of the facility since the HR model implementation.
- To identify any particular constraints experienced by women and disadvantaged groups in the community.

*In-depth interviews with District Officials,* in particular the DPHO, administrative officer responsible for HR and district supervisors. Who is interviewed will also be influenced by issues coming from facility level.

Purpose of interviews with District officials:

- To understand how well the model is being implemented, what is working well and what is not, challenges and successes.
- To identify and discuss wider context issues, such as central policy changes, resource limitations/changes, other HR interventions.
- To triangulate information from facility level.

*Reflective workshops* for Health Workers and district officials in each district will be held once a year in order to reflect on the successes and challenges of the intervention.

*Routine data collection:* The team will also collect and review health facility data and routine HMIS data through time.

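### Adjusting for other HR initiatives and health system changes cannot separate a system-wide change from the before/after effect, because all three districts get the model between the same two rounds

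*Protocol*

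**What the plan says.** The aim (Project summary; Study goal and objectives) includes effectiveness as well as process. On design:

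- Selection is "Purposive selection of 3 districts, one from each ecological zone", and "the improved HWPM will be implemented in the 3 intervention districts". No control or comparison district is named for these three.
- Study design/methodology: "The effectiveness of the model will be compared using baseline and end-line data".
- Analysis, Motivation Tool: the difference in mean score "before the intervention and after will be analysed using ANOVA to identify any significant differences". Regression on gender, age, cadre and place of work follows. Then comes the sentence at issue: "Factors such as other HR initiatives or health systems changes will also be recorded and included in the analysis as they potentially be confounders".
- Step 3 tells interviewers to look for context issues such as "central policy changes, resource limitations/changes, other HR interventions".
- Analysis, Routine Health Service Data: "Frequency tables with proportions will be used to compare secondary outcomes across districts", with five-year trends from annual reports where possible. Expected outcomes adds that these indicators are measured before the intervention and one year later.
- Step 1.1, for Doti only: at least five years of routine data, with "comparison with similar districts to see any possible improvements".

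**The concern.** A before/after contrast in districts that are all treated attributes to the model whatever else changed over the same interval. The protocol recognises this and names its statistical safeguard: measure the other changes and put them in the analysis. That safeguard fails for the most plausible rival explanation, a national one. The Background describes an HRH strategic plan that aims at worker performance through performance-related supervision, job descriptions and review processes, which are also components of the model. The section on stakeholder engagement calls that strategy still young. Its implementation during the study would act on the same levers, in all three districts, between the same two rounds.

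Two things are at stake. A reader told that system changes were adjusted for will take the motivation difference as the effect of the model. And Step 4 carries that difference into an incremental cost per change on the motivation tool, for use in national scale-up.

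**Working it through.** **1. The plan's own figure.** Inputs (Sampling): 250 analysable questionnaires per round, SD 11, difference 3 points, alpha 5%; two-sided is assumed here.

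SE = 11 × √(2/250) = 0.984. Power = Φ(3/0.984 − 1.96) = Φ(1.09) = 86.2%. The stated 86% reproduces.

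**2. What the design can separate.** 3 districts × 2 rounds = 6 cells. Intercept (1), district (2) and round (1) use 4 parameters. Adding a term for a concurrent change gives:

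| Added term | Columns | Rank | Separable from the before/after effect? |
|---|---|---|---|
| System-wide, present only at endline | 5 | 4 | No: identical to the round term |
| One district, constant over both rounds | 5 | 4 | Not estimable: duplicates a district term |
| Starts in one district between rounds | 5 | 5 | Yes, if the model effect is the same everywhere |
| Starts in two districts, separate terms | 6 | 6 | Yes, on the same assumption |
| Starts in all three, separate terms | 7 | 6 | No |

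If the change may differ by district, two district-by-round terms are needed. The model then has 6 parameters for 6 cells, and any further district-level term gives 7 columns with rank at most 6. Expected outcomes anticipates that the model will work differently in different contexts, so this case is realistic.

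**3. Price of the estimable case.** If one district has its own initiative, the round effect rests on the other two. Table 7 gives 51, 100 and 129 invited in Rasuwa, Dang and Baitadi. Scaling by 250/280, power for 3 points is:

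- initiative in Rasuwa: (100 + 129) × 250/280 = 204 per round, 79%
- initiative in Dang: (51 + 129) × 250/280 = 161 per round, 69%
- initiative in Baitadi: (51 + 100) × 250/280 = 135 per round, 61%

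**4. Factors varying between facilities.** Table 8 lists 10 + 20 + 35 = 65 facilities, and Step 4 revisits the same ones. An initiative present in some facilities of a district and not others is not confined to the six cells and can be adjusted for.

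**5. Effect of background drift.** The documents give no value, so these are assumed. With drift δ and no effect of the model, the chance of a significant result is 1 − Φ(1.96 − δ/0.984) + Φ(−1.96 − δ/0.984):

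| Assumed drift (points) | Chance of p < 0.05 |
|---|---|
| 0.5 | 8% |
| 1 | 17% |
| 2 | 53% |
| 3 | 86% |

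**6. Would a comparator survey repair the motivation test?** For illustration, assume comparators of equal size, SD 11 and no allowance for clustering. A difference-in-differences with 250 per cell has SE = 11 × √(4/250) = 1.391 and power Φ(3/1.391 − 1.96) = 58%. Restoring 86% needs 498 per cell, or 498/0.9 ≈ 554 invited. Table 8 estimates 318 available workers in the sampled facilities.

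**The case against.** The study describes itself as mixed-methods research centred on process evaluation. Interviews with district officials are to identify wider context issues, and Step 4 triangulates quantitative with qualitative findings, so part of the narrative account recommended below is already planned. This stands and lowers the stakes. It does not remove the point, because effectiveness is in the stated aim and the adjustment claim is in the protocol itself, not left to a later analysis plan.

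A reader might infer that no adjustment for concurrent events can work. The documents do not support that: steps 2 to 4 show estimable cases.

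A reader might also infer that the routine-data plan only compares treated districts with each other, or credits any secular rise in service use to the model. It does neither. The indicators are measured before and after, five-year trends are used where possible to guard against over-reading peaks, and Expected outcomes calls them secondary, collected to explore relationships over a period that may be too short to show impact. The fair description is an uncontrolled before/after contrast with a descriptive safeguard.

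Nor is the third Nepal Health Sector Programme a concurrent intervention on this text: it is described as in development. The argument rests on the HRH strategy and on the central policy changes named in Step 3.

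**Conclusion.** The concern holds in limited form. For a system-wide change present only at endline the aliasing is exact and depends on no assumption about sample size or variance. For district-level changes it holds if the effect may differ by district. With a common effect, an initiative confined to one or two districts can be adjusted for; in the one-district case power falls to between 61% and 79%. Those power figures, and the 8% to 86% range for drift of 0.5 to 3 points, assume SD 11, 250 per round and no clustering. The drift values are illustrations, not predictions.

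It is tempting to conclude that the comparison planned for Doti would give the main test its missing comparator. It would not: that comparison covers routine health outcomes, and no motivation survey is planned outside the intervention districts. For motivation, the remedy is what is claimed. The protocol should be changed on this point, but the study's process-evaluation purpose is untouched.

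**What to change.** 1. **Analysis, Motivation Tool.** Limit the adjustment sentence to factors that vary between facilities or between districts, and state the common-effect assumption where a district-level factor is entered. Report system-wide changes narratively, dated against the two rounds. Word the motivation result, and the cost per change in Step 4, as change over the period and not as effect of the model. Cost: wording only.

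2. **Analysis, Routine Health Service Data.** Extract the same HMIS or annual-report series for similar non-intervention districts, as Step 1.1 does for Doti, and report the difference in change beside the five-year trends. Label it exploratory: there are only three treated districts, purposively chosen, and comparators may differ from them. Cost: desk extraction for a few more districts and a modest analysis, with no new participants. An interrupted time series on monthly counts is not proposed, because the documents do not establish that monthly series are available.
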